### Data Collection and Randomization

Survey and interview data in Ottawa and Toronto are being collected at multiple time points over the course of 4 years to capture a range of outcomes, as listed in Table 1. Data collection is expected to be completed at both sites by March 2024. The data collection procedures follow a sequential, mixed methods design [38], which involves a 2-phase process starting with the quantitative data collection, followed by a qualitative phase to help provide a deeper understanding of the survey responses and quantitative results based on participants’ personal narratives and life journeys through homelessness.

**Table 1 table1:** Core outcome areas, domains, measures, and interval schedule.

Core outcome areas, variables, and domains			Measures and instruments		Interval
**Housing stability^a^**					
	Obtaining and maintaining housing with reduced stays in emergency shelters	Residential timeline follow-back [39]^b^		3 months^c^	
	Knowledge and skills regarding housing and independent living	Casey-Ansell Youth Life Skills Assessment (adapted) [40]		6 months	
**Health and well-being^a^**					
	Perceptions of health and well-being	World Health Organization Quality of Life-Brief Form [41]		6 months	
	Behavioral health	Global Appraisal of Individual Needs–Short Screener [42]		6 months	
	Food security	Food Security Survey [43]		6 months	
	Psychological functioning	Brief Symptom Inventory [44]		6 months	
	Substance use patterns	Ontario Student Drug Use and Health Survey [45]		6 months	
	Self-efficacy	General Self-Efficacy Scale [46]		6 months	
**Complementary supports^a^**					
	Life skills	Casey-Ansell Youth Life Skills Assessment (Adapted) [40]		6 months	
	Access to necessary nonmedical services	Diagnostic interview		6 months	
	Hope for the future	Herth Hope Index [47]		6 months	
	Legal and justice issues	Diagnostic interview		6 months	
	Resilience	The Resilience Scale-14 [48]		6 months	
**Education and employment**					
	Participation in education and training	VTLFB^d^ and education [13]		3 months	
	Educational achievement	Diagnostic interview		24 months	
	Participation in the labor force	VTLFB and employment		3 months	
	Financial security	VTLFB and income		3 months	
**Social inclusion**					
	Family and natural supports	Multidimensional Screener of Perceived Social Support		6 months	
	Sense of belonging to the community	Psychological Community Integration Scale [49]		6 months	
	Engagement in cultural and meaningful activities	Physical Community Integration Scale [50]		6 months	

^a^Primary outcomes domains.

^b^The residential timeline follow-back (RTLFB) is designed to assess various aspects of housing status and stability. In this study, it serves to incorporate point-in-time assessments and longitudinal evaluations of participants’ housing stays and transitions. It allows building a chronological record of each respondent's residential history between successive interviews. In addition, the RTLFB collects information about the type of residence, the individuals the participants are living with, and the reasons for moving in and moving out during the specified period. The records obtained from the RTLFB will be analyzed to gain insights into the specific places where young people stayed during the study, as well as the reasons for their moves in and out of different residences. This information will contribute to a comprehensive assessment of the effectiveness and impact of the HF4Y intervention on their housing stability and overall well-being.

^c^The measures and intervals listed will be used at the interval indicated to collect data over 48 months (eg, the residential timeline follow-back is being used every 3 months for 48 months).

^d^VTLFB: vocational timeline follow-back.

It was expected that baseline differences would exist across sites, reflecting the diverse demographic, socioeconomic, and ethnoracial background of participants based on regional characteristics. To achieve representativeness in the RCT sample, homogeneous sampling was used [38], which targeted several shared characteristics including age range (youth aged 16-24 years) and those who were experiencing homelessness or were at risk of homelessness. For each site, a minimum of 63 participants needed to be recruited for the study to be able to detect an effect size of 0.5 between the TAU group and the intervention group for the primary outcome domains, given α=.05 and β=.20. However, the total number of participants recruited was 148 to account for an attrition rate of 25%, following similar RCT-designed studies [11,17].

The participants were assigned through strict randomization to either the TAU or HF intervention groups. Research assistants sealed assignments in envelopes ordered by participant identification number according to a randomization sequence generated through a web-based random sequence generator. Once the baseline interview was completed, the participants received a notification of the group assignment in a sealed envelope along with an information sheet. In Ottawa, 44 youths were assigned to the HF intervention group and 42 were assigned to TAU group. In Toronto, the number of participants in the HF intervention and TAU groups was equal (n=31; Figure 1). After group assignment, research assistants connected the participants assigned to the HF intervention group to the program service provider. Participants randomized to the TAU group were informed about the available services in the community. All participants were informed of the schedule of research follow-up appointments and were invited to use the research field office or the participating service agency as a resource center. All participants were provided with a pamphlet on existing services in the community.

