### Participant Retention

Participation retention is a major concern, particularly in RCT studies where receiving maximum response rates and compliance with the research protocol is pivotal to their success. In this longitudinal study, enrolling young people experiencing homelessness and housing precarity was a particularly difficult task because of their involvement in a variety of competing activities, such as school and meeting their basic needs. In addition, barriers such as unstable housing and frequent transitions have made it difficult for youth to maintain a consistent mode of communication over time. The COVID-19 pandemic in February 2020 compounded these challenges, as it disrupted the efforts made to establish and maintain contact with youth.

Existing literature suggests strategies to minimize participant attrition, which broadly include baseline tracking procedures such as collecting detailed information on the participant’s location and follow-up procedures, including sending reminders to conduct follow-up interviews [51-53]. Consistent with the literature, this study uses an array of techniques to maintain contact with hard-to-reach participants, which include building rapport, supplementing traditional tracking methods (eg, phone, email, social media, and known associates) with new technologies, and offering financial incentives. More importantly, as data collection is still underway, a key factor is cultivating an appreciation of the contribution of the respondents as experts. Such a “participant-centered” approach [54] ensures that participants are aware of the impact of their participation in the outcomes and success of the study, thereby increasing the likelihood that they will continue to be engaged in the study. Although the existing body of research suggests varying rates of retention depending on the types of strategies used, ranging from 65% to 85% [53], this study aims to keep approximately 75% of the participants engaged in the study over 4 years.

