### Analytical Procedures

HF intervention and TAU groups will be compared within each RCT site; although if it is determined that no significant differences exist between the 2 sites in terms of sociodemographic characteristics and outcome measures collected at baseline, the TAU and intervention groups will be combined accordingly across sites to increase the power of the study. There will be an interim analysis using 2-year quantitative data, with the final analyses based on the 4-year data. It is expected that certain participants might not adhere to the protocol or could discontinue their involvement owing to health issues or fatigue arising from repeated assessments. As deviations from the protocol are inevitable and likely to occur in real-time practice [58-60], there exist a number of approaches that can preserve the integrity of the randomization process including an intention-to-treat analysis, which considers all participants initially randomized in the study.

In addition, certain participants may be more likely not to respond to surveys, or certain questions might be more likely to have missing responses. With respect to missing data, 3 common mechanisms can be observed: missing completely at random, missing at random, and missing not at random [61,62]. For data missing completely at random, single imputation methods can be used to address the missing values, albeit with a tendency to provide conservative estimates of the treatment effect; for example, missing values can be replaced with the last observed values or the mean values. For data missing at random and missing not at random, multiple imputation can be used, which produces a more accurate and less biased estimate of the treatment effect [63].

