For continuous outcome measures, differences between the intervention and control groups will be examined by using mixed-effects modeling for repeated measures. For binary outcomes, logistic models will be used, and negative binomial modeling will be used for all count outcome measures to account for any possible overdispersion in the data. Sociodemographic characteristics collected at baseline will be entered into the models as covariates, and the interaction between time and intervention will be considered to capture the interaction effects. All quantitative analyses will be conducted in SPSS (IBM Corp) and R studio (Posit) software packages with power set at 80% (α=.05 and β=.20) to detect an effect size of 0.5 between the TAU and intervention groups for the primary outcome domains.

Qualitative data will be assessed through thematic analyses to identify common themes related to outcomes and to analyze the underlying intervention process, consistent with the approaches suggested by Miles et al [64] and Saldaña [65]. The qualitative data provide a rich source of the narratives regarding young people’s experiences with homelessness, housing instability, and interaction with the HF4Y program itself. Interviews will be transcribed and imported into NVivo (QSR International) software for analysis. Rather than focusing on preexisting theoretical constructs using an a priori method, an emergent, bottom-up approach will be used for coding [64]. The process of coding will shift back and forth from the key narratives provided by the participants to the researcher’s interpretation of the meaning of those narratives, which will be documented through the researcher’s analytic memos. Recurring patterns gleaned from the codes will be grouped as themes and will be thematically classified under broader themes. The final set of themes will be summarized and presented in a table, where representative quotes from transcripts will be paired with themes as textual evidence.

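### The minimum of 63 participants per site does not support 80% power for the within-site comparison; at an effect size of 0.5, 63 is the number needed per arm

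*Protocol article*

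**What the plan says.** The sample-size statement is in Methods, Data Collection and Randomization, in the text after Table 1: "For each site, a minimum of 63 participants needed to be recruited for the study to be able to detect an effect size". The size in question is 0.5, comparing the two arms on the primary outcome domains, and the error rates are stated as "given α=.05 and β=.20". The same paragraph gives 148 as the total recruited and 25% as the attrition allowed for. It also says that the sites were expected to differ at baseline.

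The arm sizes follow in the same section: 44 and 42 in Ottawa, and "In Toronto, the number of participants in the HF intervention and TAU groups was equal (n=31; Figure 1").

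Analytical Procedures sets the default comparison: "HF intervention and TAU groups will be compared within each RCT site". Pooling across sites is allowed only if the sites show no significant baseline differences, and it is presented as a way to gain power. That section also repeats the claim, "with power set at 80% (α=.05 and β=.20) to detect an effect size of 0.5 between the TAU and intervention groups". Participant Retention gives the matching target: "this study aims to keep approximately 75% of the participants engaged in the study over 4 years".

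**The concern.** At a standardised difference of 0.5, two-sided α of .05 and 80% power, 63 is the familiar per-arm answer for two independent groups. The article gives it as the number for a whole site, which is then split between two arms, and names the site as the unit of comparison. For that comparison the stated number is about half of what the stated inputs require.

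What is at stake is how site-level results are read. The article plans 24-month and 48-month reports for all levels of government. Readers who take 80% power at face value could give a non-significant result at one site more weight against a moderate effect than the design supports.

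**Working it through.** **Inputs.** Effect size 0.5, read as a standardised difference; α=.05; power 80%; 63 per site; 148 recruited; 25% attrition (Data Collection and Randomization; Analytical Procedures; Participant Retention). Arm sizes: Ottawa 44/42, Toronto 31/31. Pooled: 44+31 = 75 against 42+31 = 73. Assumption: two-sided α.

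**Step 1: reproduce 63.** n per arm = 2(z₀.₉₇₅ + z₀.₈₀)²/d² = 2(1.960 + 0.842)²/0.5² = 62.8, so 63 per arm and 126 per comparison. The t distribution gives 63.8, so 64 per arm and 128 per comparison. Other variants do not give 63 as a two-arm total:
- One-sided α: 50 per arm, 100 per comparison.
- One-sample or paired test: about 34.
- Two-group ANOVA: 128 in total with f=0.25, about 34 with f=0.5.

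**Step 2: power at d=0.5.** Normal approximation: Φ(d√[n₁n₂/(n₁+n₂)] − 1.960). For Ottawa with no loss: 0.5√(44×42/86) = 2.318; 2.318 − 1.960 = 0.358; Φ = 0.64. The noncentral t gives 0.63. After attrition each arm is multiplied by 0.75.

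| Comparison | Arms | Normal | t |
|---|---|---|---|
| One site of 63 | 32/31 | 51% | 50% |
| Ottawa, no loss | 44/42 | 64% | 63% |
| Ottawa, 25% loss | 33/31.5 | 52% | 51% |
| Toronto, no loss | 31/31 | 50% | 49% |
| Toronto, 25% loss | 23.25/23.25 | 40% | 39% |
| Pooled, no loss | 75/73 | 86% | 86% |
| Pooled, 25% loss | 56.25/54.75 | 75% | 74% |
| 63 per arm | 63/63 | 80% | 80% (79.5%) |

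**Step 3: effect detectable with 80% power (t).** With no loss: Ottawa 0.61, Toronto 0.72, pooled 0.46. After 25% loss: Ottawa 0.71, Toronto 0.84, pooled 0.54.

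**Step 4: attrition.** To keep 126 after 25% loss, 126/0.75 = 168 must be recruited. The actual 148 leaves 148×0.75 = 111. Toronto's 62 is also one short of the stated minimum before any loss.

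**Step 5: sidedness.** With one-sided α=.05, t-based power is 62% for 32/31. Ottawa has 74% with no loss and 63% after it; Toronto has 62% and 51%. Pooled after loss it is about 84%. No single-site value reaches 80%.

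**Step 6: what the planned model might add.** For 63 per site to give 80%, the variance must fall to 63/125.6 = 0.50 of its single-visit value. If the outcome is averaged over m visits with constant within-person correlation ρ, the factor is (1+(m−1)ρ)/m. Table 1 implies 48/6 = 8 or 48/3 = 16 follow-ups. With assumed ρ of 0.3 to 0.7 and m of 4 to 16, power after 25% loss runs from about 63% to 93% in Ottawa and 49% to 83% in Toronto (normal approximation). At m=8 and ρ=0.5 the factor is 0.5625, giving 76% and 62%.

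**The case against.** Three arguments have weight.

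First, the article names no formula. The sentence can be read as 63 at each of two sites, 126 in all, to power the study as a whole. Pooled, that gives 79.5%, in effect the stated figure. A reader might infer that a per-arm number was certainly mistaken for a site total. The arithmetic points that way, but the documents do not settle where the figure came from. The pooled reading still does not make the statement right: the default comparison is within site, pooling is conditional, and baseline differences between sites were expected. With two-sided α, the 111 retained would give 74% even if pooled.

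Second, the planned analysis of continuous outcomes is a covariate-adjusted mixed model over many visits, not a t-test at one visit. It also uses the earlier visits of participants who later drop out, so treating 25% attrition as complete loss is pessimistic. This stands as a limit on the size of the problem. It does not justify 63, which is exactly what the simple formula gives with no repeated-measures gain. Nor do the t-test figures describe the binary and count outcomes. Leaving a correlation to a fuller document is ordinary practice and is not the complaint here.

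Third, the study calls itself a pilot and lists low sample size as a limitation. That is candid, but it does not withdraw the 80% claim, which appears twice.

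**Conclusion.** The point holds: 63 per site is not supported for the comparison the plan makes by default. On the article's own inputs with two-sided α, 63-64 per arm are needed. Single-site power at 0.5 is 63% and 49% with no loss (Ottawa, Toronto), and 51% and 39% after 25% attrition. Pooled power is 86%, falling to 74%. One-sided α raises these figures but leaves both sites below 80%.

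A reader might go further and call 39% to 51% the true power of the trial, or say that its site comparisons are no better than a coin toss. The documents do not support that. Those figures are two-sided, unadjusted and for one time point; the planned model's power depends on an unstated correlation and could be materially higher. Nor should the figures be merged into one range from about 40% to 63%, since its ends rest on different attrition assumptions. Equally, nothing in the article establishes 80% at either site.

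**What to change.** Correct the sample-size statement in Data Collection and Randomization and its repetition in Analytical Procedures:

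- State that 63-64 participants per arm (126-128 per comparison) are needed for 80% power at 0.5 with two-sided α=.05, and say whether two-sided is what was intended.
- Withdraw the 80% claim for single-site comparisons.
- Report within-site and pooled power, or detectable effects, labelled as two-sided, single-time-point and unadjusted, with and without the 25% attrition.
- Limit any power claim to the pooled comparison and give its attrition-adjusted value: about 74% at 0.5, or 80% at 0.54, with 111 retained. Note that pooling is itself conditional under the plan.
- If power is to be claimed from the repeated-measures model instead, recompute it and state the sidedness, within-person correlation and number of visits used.

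Recruitment is closed and no extra participants are needed. The change is to the text and, on the last route, one recalculation. The only cost is a less favourable stated power.

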To identify eligible participants to be recruited for the study, outreach activities began with local agencies and providers who were in contact with young people experiencing homelessness in Ottawa. Community representatives from each site developed a strategy to work with potential referral sources and inform them about the study. Strategies to ensure adequate participation in the study included seeking referrals from a wide range of services accessed by each site population. In Ottawa, these included local youth shelters, drop-in centers, city prioritization lists (ie, by-names list), and other local service agencies delivering programs for youth experiencing homelessness. In Toronto, youth were primarily referred by Youth in Transition workers who work with youth exiting the child welfare system, in addition to the types of referral sources used in Ottawa. Researchers and service delivery teams followed site-specific strategies for informing referral agencies (eg, outreach, posters, and meetings with key staff), identifying prospective participants, making contact to ascertain participant interest, and carrying out screening processes.

Recruitment for the study started in February 2018 in Ottawa and was completed in November 2019, with 86 participants enrolled in the study. In Toronto, the first participants were recruited in June 2018, and the final group of youth was admitted to the study in March 2020, with 62 youth participants in total. At the initial interview, participants were guided through an informed consent process and then asked to complete a baseline evaluation (interview and survey) before receiving a notification of the group assignment.

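### The 148 recruited do not cover 25% attrition on the plan's own figures, and the 63 per site behind them is a per-arm number

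*Protocol article*

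**What the plan says.** The sample size paragraph under Data Collection and Randomization states: "For each site, a minimum of 63 participants needed to be recruited for the study to be able to detect an effect size of 0.5". The error rates there are "given α=.05 and β=.20". It goes on to say that "the total number of participants recruited was 148 to account for an attrition rate of 25" per cent.

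Participants' Recruitment gives the split. Ottawa "was completed in November 2019, with 86 participants enrolled in the study"; in Toronto "the final group of youth was admitted to the study in March 2020, with 62 youth participants in total". The arm sizes under Data Collection and Randomization (44 and 42 in Ottawa, 31 and 31 in Toronto) agree with these totals. Participant Retention repeats the attrition assumption from the other side: "this study aims to keep approximately 75% of the participants engaged in the study over 4 years".

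Analytical Procedures makes the comparison within each site the default. It pools the sites only if they do not differ significantly at baseline, and the sample size paragraph itself expects such differences. The same section then describes the analyses "with power set at 80% (α=.05 and β=.20"), for the same effect size and the same primary domains, without conditions.

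**The concern.** The reader is told that recruitment was set high enough to absorb the expected loss and that 80% power holds. Two things do not fit. First, no standard inflation of 63 per site for 25% loss gives 148, and one site did not reach 63 at all. Second, 63 is familiar as the number per arm for a half-standard-deviation difference, yet the article attaches it to a whole site containing both arms.

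This bears on how a null result is read. If the sites are analysed separately, a non-significant result in either could be taken as evidence of no effect from a comparison believed to have 80% power, when its power may be nearer one half or less.

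**Working it through.** **Inputs.** From the article: effect size 0.5, alpha .05, power 80%, 63 per site, two sites, 25% attrition, Ottawa 86 (44/42), Toronto 62 (31/31). Assumed, because the article does not say: the effect size is a standardized mean difference, and tests are two-sided.

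**1. Reproducing 63.** n per arm = 2(z₀.₉₇₅ + z₀.₈₀)²/d² = 2(1.960 + 0.842)²/0.25 = 62.8, so 63 per arm (63.8, so 64, with the t distribution). One two-arm comparison therefore needs 126. A one-sided test would give 50 per arm, so the two-sided assumption is the one that yields the printed 63. The figure reproduces as a per-arm number, not as a site total.

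**2. The attrition step.**
- Correct inflation: 63/0.75 = 84 per site; 126/0.75 = 168 in total.
- Cruder inflation: 63 × 1.25 = 78.75, so 79 per site; 126 × 1.25 = 157.5, so 158 in total.
- Retained from 148: 148 × 0.75 = 111, which is 15 below 126.
- Loss that 148 tolerates: 1 − 126/148 = 14.9%.

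The answer is the same whether 126 is read as two sites of 63 or as two pooled arms of 63.

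**3. By site.** Ottawa: 86 × 0.75 = 64.5, above 63. Toronto: 62 × 0.75 = 46.5, below 63, and 62 < 63 before any loss. The two sum to 111.

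**4. Power at d = 0.5.** Two-sided two-sample t-test, noncentrality d/√(1/n₁ + 1/n₂), n₁ + n₂ − 2 degrees of freedom. The 25% loss is applied equally to both arms. Detectable d is at 80% power.

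| Comparison | n per arm | Power | Detectable d |
|---|---|---|---|
| One site at the stated 63 | 31/32 | 50% | |
| Pooled, 126 | 63/63 | 79.5% | |
| Pooled, 148, no loss | 75/73 | 86% | |
| Pooled, 111, after loss | 56.25/54.75 | 74% | 0.54 |
| Ottawa, no loss | 44/42 | 63% | |
| Ottawa, after loss | 33/31.5 | 51% | 0.71 |
| Toronto, no loss | 31/31 | 49% | 0.72 |
| Toronto, after loss | 23.25/23.25 | 39% | 0.84 |

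**5. Separating the two errors in Toronto.** Treating a per-arm number as a site total takes power from 80% to about 50%, some 30 points. Having 46.5 rather than 63 at the end takes it from 49.7% to 38.5%, about 11 points. Full inflation to 84 with 63 retained would still have given only about 50%.

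**6. What the planned models might recover (assumed correlations).** Adjusting for a baseline value with correlation r multiplies 126 by (1 − r²): about 115 at r = 0.3, 95 at 0.5 and 64 at 0.7. Averaging m follow-ups with intraclass correlation ρ multiplies it by (1 + (m − 1)ρ)/m: from about 107 (m = 2, ρ = 0.7) down to 43 (m = 16, ρ = 0.3). The second calculation concerns an average over follow-up, not the 48-month difference.

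**The case against.** The strongest reply is that completer counts are the wrong yardstick. Analytical Procedures foresees mixed models for repeated measures, baseline covariates and multiple imputation, and mentions intention-to-treat, so participants who leave early still contribute data. Under some of the correlations in step 6, 111 would be ample pooled, and in the most favourable corner even Toronto's 46.5 would be enough. This stands as a limit on the power figures. It does not rescue the attrition sentence: 63 is the plain two-sample number, and no correlation is stated.

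It is also fair that the pooled loss is modest: 79.5% at 126 against 74% at 111, about 5 points. Toronto's miss before attrition is one participant, worth 49.1% against 49.7%. Strengths and Limitations does admit small sample size and dropout as weaknesses, but it neither withdraws the attrition claim nor says that a site missed its minimum.

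A one-sided test with pooling would make 148 sufficient (100/0.75 = 134), but it gives 50 per arm, not 63.

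Three stronger inferences are tempting, and the article does not support them:
- That Toronto's 39% is the price of attrition. Most of it comes from using a per-arm number as a site total.
- That Ottawa is safe because 86 exceeds 84. It meets the article's site figure, but that figure does not deliver 80% power within a site.
- That 39% or 74% is the power of the planned analysis. They are two-sample completer figures.

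**Conclusion.** The statement that 148 accounts for 25% attrition is wrong as written: 168 would be needed, 148 leaves about 111, and the loss it tolerates is 14.9%. Toronto did not reach the stated site minimum. This part follows from the article's own numbers and needs no assumption about the test.

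The larger consequence is that 63 is a per-arm figure. On a two-sided, standardized-difference, two-sample basis with equal loss in both arms, the default within-site comparison has about 50% power at 63. It has about 51% in Ottawa and 39% in Toronto after loss; the pooled comparison has about 74%. The unconditional 80% therefore does not hold on that basis for any of the three after the expected loss. Before loss it holds only pooled (86%), and pooling depends on the sites not differing at baseline.

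This is not evidence that the final analysis must be underpowered to this degree. Repeated measures and baseline covariates could recover power by an amount the article does not allow one to quantify.

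**What to change.** Under Data Collection and Randomization, delete the claim that 148 covers 25% attrition and replace it with text on these lines:

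- Detecting d = 0.5 with two-sided alpha .05 and 80% power needs 63 per arm, that is 126 for one two-arm comparison.
- In all, 148 were recruited (Ottawa 86, Toronto 62). With 25% attrition about 111 are expected at 48 months (64.5 and 46.5 by site).
- For a two-sided two-sample comparison of completers at d = 0.5, power before and after loss is about 86% and 74% pooled (detectable d after loss 0.54), 63% and 51% in Ottawa (0.71), and 49% and 39% in Toronto (0.84).
- The repeated-measures models with baseline covariates may recover some power; no correlation is available here to quantify it.

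Do not keep 63 as a valid minimum per site. Qualify the 80% power statement under Analytical Procedures to match.

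The cost is a few sentences and a less favourable account of power. Enrolment and conduct do not change, since recruitment closed in March 2020.

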Within the Canadian context, the national At Home/Chez Soi project initiated in 2008 the largest randomized controlled trial (RCT) of the Housing First intervention, with many studies stemming from this research project [10-15]. The Mental Health Commission of Canada implemented the Housing First model in 5 cities (Vancouver, Winnipeg, Toronto, Montreal, and Moncton) with >2200 individuals who were experiencing homelessness. The 1-year and 2-year findings of the At Home/Chez Soi project across various sites provided compelling evidence that the Housing First intervention is an effective approach that helps individuals experiencing homelessness and who have serious mental illnesses exit homelessness more quickly compared with other treatment-as-usual (TAU) services [11,12,16,17].

However, as discussed by Goering et al [10], it remains unknown whether the Housing First intervention is effective and can be replicated among young adolescents with diverse racial and sociodemographic backgrounds, particularly within the Canadian context where Indigenous youth experiencing homelessness are overrepresented [3]. In addition, although Kozloff et al [14] presented promising results that the Housing First model can be “a viable intervention to promote housing stability in homeless youth with mental illness,” they suggested that modifications be made to the model to better meet the needs of youth, as their findings indicated that the application of the model to young people did not significantly improve other primary outcomes in the treatment group (eg, community integration and substance use).

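### The 25% attrition allowance is weakly supported for a 4-year analysis, and the stated 80% power is not reached even if it holds

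*Protocol article*

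**What the plan says.** The sample size is in Data Collection and Randomization, in the paragraph after the notes to Table 1. The requirement is set by site: "For each site, a minimum of 63 participants needed to be recruited for the study". The difference to be detected between arms is 0.5, at a 5% significance level and with 80% power. The total of 148 is then explained as being there "to account for an attrition rate of 25%, following similar RCT-designed studies [11,17".

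The Background section cites references 11 and 17 once more, in a sentence that begins "The 1-year and 2-year findings of the At Home/Chez Soi project across various sites provided compelling evidence" and ends "compared with other treatment-as-usual (TAU) services [11,12,16,17".

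Participant Retention mentions published retention of 65% to 85%, without saying over what length of follow-up, and then states that "this study aims to keep approximately 75% of the participants engaged in the study over 4 years".

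Analytical Procedures plans an interim analysis at 2 years and final analyses on the 4-year data. Arms are compared within each site, and sites are pooled only if they do not differ at baseline. The power claim is repeated there: "with power set at 80% (α=.05 and β=.20) to detect an effect size of 0.5", with no time point attached.

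**The concern.** The attrition allowance should match the time point it protects. Here the cited support comes from a group of references linked to 1-year and 2-year results, and it is carried unchanged to 48 months. The article itself gives reasons to expect difficult follow-up: unstable housing, frequent moves, contact disrupted by the pandemic, and a weaker incentive to attend in the control arm. It gives no reason why loss would stop after year 2.

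At stake is how the 4-year result is read. The 80% figure appears twice without qualification. A reader who applies it to a non-significant 4-year comparison would take that result as better evidence against a 0.5 SD effect than the remaining sample can provide.

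**Working it through.** **Inputs (all from the Protocol article).** Effect size 0.5, taken as standardized; α = 0.05; power 0.80; attrition 25%; cited retention range 65% to 85%, so loss of 15% to 35%. Allocation is 44 and 42 in Ottawa and 31 and 31 in Toronto, so 75 and 73 pooled. Sidedness is not stated; two-sided is assumed.

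**Reproducing 63.** The normal-approximation formula for two means is n per arm = 2(1.96 + 0.84)²/0.5² ≈ 62.7, rounded up to 63. So 63 is the number per arm, or 126 per comparison (64 and 128 with the exact t-test). A one-sided test would need 50 per arm, so 63 matches the two-sided per-arm number. The article applies it to a whole site. A site of 63 in total has two-sided power of about 0.50.

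**Reproducing 148.** Allowing for 25% loss, 126/0.75 = 168 for one pooled comparison. Two sites of 63 give 2 × 63/0.75 = 168 as well. In the other direction, 148 × 0.75 = 111, which is below 126. So 148 does not follow from the stated inputs.

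**Power at d = 0.5.** Two-sided noncentral t, with the actual arm sizes multiplied by (1 − loss):

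| Loss | Pooled N | Pooled | Ottawa | Toronto |
|---|---|---|---|---|
| 0% | 148 | 0.86 | 0.63 | 0.49 |
| 15% | 126 | 0.79 | 0.56 | 0.43 |
| 25% | 111 | 0.74 | 0.51 | 0.39 |
| 35% | 96 | 0.68 | 0.45 | 0.34 |
| 43.75% (assumption) | 83 | 0.62 | 0.40 | 0.30 |

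The last row is not a figure from the documents. It assumes 25% loss in each 2-year period at a constant rate: 1 − 0.75² = 0.4375.

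**Effect detectable with 80% power, pooled.** d = 2.8 × √(4/N):
- 15% loss: 2.8 × √(4/125.8) = 0.50
- 25% loss: 2.8 × √(4/111) = 0.53
- 35% loss: 2.8 × √(4/96.2) = 0.57
- 43.75% loss (assumption): 2.8 × √(4/83.25) = 0.61

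**Separating the two causes.** Within a site, power is below 0.80 with no loss at all (0.63 and 0.49). Pooled, it is 0.74 at the plan's own 25%. Moving from 25% to 35% loss costs a further 0.06 pooled, 0.06 in Ottawa and 0.05 in Toronto. Most of the shortfall therefore comes from using the per-arm number per site; uncertainty about attrition adds to it.

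**The case against.** The strongest reply is that 25% is an explicit 4-year planning figure. Participant Retention sets about 75% over 4 years as the aim, at the middle of a cited range, and backs it with tracking, rapport-building and payments. That stands as far as it goes. It is a target, however, and the range behind it has no stated follow-up length.

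A reader might go further and infer that the 48-month sample and power are overstated because of where the 25% came from. The documents do not support that. They give neither the loss seen in references 11 and 17 nor any 4-year loss in this trial. If loss in those studies was mostly early, or below 25%, the 4-year figure could be near 25%. Nor can the 25% be compounded from a 1-year figure: four references are cited together for the 1-year and 2-year findings, so it cannot be told which is which. The 44% row is a scenario only.

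The calculation is also simpler than the planned analysis. Mixed-effects models use partial follow-up, and baseline adjustment can add precision, so the true power may be somewhat higher. For 63 per site to suffice, though, the correlation with baseline would have to be about 0.71 (√(1 − 63/126)), and no such assumption is stated. With a one-sided test, pooled power at 25% loss would be about 0.84 (normal approximation), but Ottawa and Toronto would still have only 0.64 and 0.52.

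Finally, recruitment has closed, and the limitations section already mentions dropouts and small sample size. So the design cannot change, but the 80% statement still stands beside those caveats without qualification.

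**Conclusion.** The point holds in two parts. First, the 25% is weakly supported for the 48-month analysis and may be optimistic; the direction and size of any error are not established. Second, the 80% power at 0.5 is not delivered at the plan's own 25%: 0.74 pooled, 0.51 in Ottawa and 0.39 in Toronto, falling to 0.68, 0.45 and 0.34 at 35%. The second part does not depend on resolving the first.

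These figures assume a standardized effect of 0.5, a two-sided test at 0.05, equal loss in both arms, and a single-time-point comparison of those remaining. They are therefore a somewhat pessimistic guide to a repeated-measures analysis.

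**What to change.** In Data Collection and Randomization and in Analytical Procedures, replace the unqualified 80% claim as follows:

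1. State that 63 is a per-arm number.
2. Give power and detectable effect for the 4-year analysis, pooled and by site, over the article's own range of 15% to 35% loss. Pooled, the detectable effect is about 0.50 to 0.57 SD. Add about 44% loss only as a labelled assumption (25% per 2 years at a constant rate; pooled power 0.62, detectable effect 0.61 SD).
3. Describe 25% as a target, and update the projection with observed 24-month retention by arm, which should be obtainable because that analysis is underway.
4. Note that a mixed model using partial follow-up may do somewhat better than these figures.
5. State that a non-significant 4-year result will be interpreted from its confidence interval, not against the 80% figure.

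The cost is a rewritten power paragraph, a matching edit where the claim is repeated, and a less favourable stated power. No further enrolment is needed.
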